### 3.3. Sample Size Calculation

Two independent HW groups will be assessed across three time points. An estimated 55 staff in each group (110 total) is required to achieve at least 80% power to detect a difference in the outcome measures as a response to the intervention. Applying the Bonferroni correction, the significance level for each test is adjusted to α = 0.05/9 = 0.0056. To assess HCs, initial power calculations suggested that for each HC group, a sample size of 50 per group per timepoint in each ward (300 participants) would result in a confidence interval limit of ±0.139 or 13.9% on a result of 0.5 or 50%. However, we expect that it would be difficult to achieve a sample size of >25 per group. The validity assessment will guide decisions regarding whether combining the two HC groups (patients and support persons) into one HC group per ward per timepoint is advisable. This part of the study is subject to modification and treated as exploratory. Power calculations were conducted in G*Power Version 3.1.9.4 for Windows.

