### 2.2. Participants

A convenience sample of HW and HC participants will be recruited to complete the study. Participants must provide written, informed consent before any study procedures occur. Eligibility criteria will differ across groups.

HW participants will consist of both registered and non-registered staff, including pharmacists, physiotherapists, occupational therapists, social workers, nurses, doctors, health care assistants, ward clerks, and domestic services staff. With an estimated drop-out rate of 25%, we will recruit up to 138 healthcare worker participants to ensure completion of 110 (55 per ward). Inclusion criteria for healthcare worker participants include (a) being employed in the clinical sites and (b) giving informed consent. Exclusion criteria include (a) working across both the intervention and control wards; (b) agency staff working across multiple wards; or (c) being a medical student, a nursing student, or an allied health student.

HC participants will consist of hospitalised patients and their visiting support persons. With an expected non-completion rate of 10%, we will recruit up to 165 participants to ensure completion of 150 (75 per ward with 25 per timepoint) to complete the study. Inclusion criteria for healthcare consumer participants include (a) ability to understand, read and write English; (b) capacity to give informed consent; (c) (for patients only) being ready for discharge—this is to allow patients to reflect on their experiences and interactions in a non-acute phase of their illness; and (d) (for support persons only) have been actively supporting the patient during their admission (i.e., visited patient at least once per week). Exclusion criteria include (a) being unable to give informed consent; (b) being under the age of 18 years; (c) (for patients only) not predicted to be discharged from the ward between the data collection periods; and (d) (for support persons only) have not been involved in regular support of the patient (i.e., visited less than once a week).

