The *Professional Quality of Life Scale (ProQOL)* [29] consists of two aspects of one’s feelings about their professional life: a positive (compassion satisfaction) and a negative aspect (compassion fatigue). Compassion satisfaction reflects the pleasure and satisfaction a person derives from their ability to do their work well and to be an effective caregiver. Compassion fatigue is divided into two parts. The first part assesses psychological aspects typical of burnout (e.g., exhaustion, frustration, and depression). The second part focuses on work-related, secondary exposure to extremely stressful events, known as secondary trauma. Each subscale is psychometrically unique and hence does not yield a composite score. Each subscale consists of 10 items, and participants are asked to rate the frequency of their experiences from 1 (*Never)* to 5 (*Very often)*. Items will be averaged together to create three distinct scales. Higher scores will indicate greater work-related satisfaction; a greater risk for job related burnout; and a greater exposure to secondary traumatic stress.

Additionally, at three time points, HW participants will provide answers to open-ended questions about aspects of their professional life related to empathy, for instance, describing their ability to empathetically relate to others in the workplace, sharing the most challenging aspect of expressing empathy towards others and if there is anything that they would like to improve about their ability of relating to others. Qualitative analyses of these written responses will be used to complement the quantitative data on understanding the efficacy outcomes of the EmpEd.

The secondary efficacy outcomes focus on HCs’ experiences of the healthcare team’s empathetic care and support over time. The same survey tools will be administered to HCs who will differ across time points:

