### 3.4. Data Management and Analysis Plan

*Qualitative analysis.* Thematic analysis will be conducted on the feasibility of the EmpEd. The analytic interest is on how the experiences of participants are located within the wider socio-cultural context of the ward, which makes thematic analysis a suitable method for our purpose [34]. Thematic analysis will identify themes addressing feasibility issues, for instance, the usefulness of the programme, staff engagement and sustainability. Interview recordings and observational notes will be transcribed. To ensure consistency and accuracy of the analysis, two members of the research team will jointly analyse the data. The thematic analysis will follow Braun and Clarke’s [35] approach and will be completed by using NVivo 12.

The confidence in the quality of the qualitative data, analysis and interpretation will be assured by following the principles of trustworthiness in qualitative research [36]. Trustworthiness will be achieved by ensuring that multiple researchers have oversight of the data collection and analysis process. To ensure credibility of the data, only HWs who have participated in the EmpEd will be recruited into the focus groups, and verbatim quotes from these participants will be used to support themes/subthemes. The use of NVivo 12 to code the data will enhance opportunities for all researchers to evaluate the process of theme development, and it will also facilitate reflection on the analysis process.

*Quantitative analysis.* Descriptive and inferential statistical analysis will be conducted to assess the feasibility and potential efficacy of the EmpEd. Online responses will be registered through Qualtrics. Hard copy survey responses will be manually entered and error checked by looking at ranges and correlations. A minimum response rate of approximately 75% will be used as a cut-off point for the analysis (i.e., lack of completion of the empathy measures). Descriptive statistics will be summarised by using a number of observations, mean, and standard deviation for continuous data, and frequency and percentage for categorical data. To explore efficacy outcomes, nonparametric analyses will be conducted across time points and between groups due to the potential of a small sample size. Missing data will be reported as missing. All statistical analyses will be performed using R Statistical software.

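### Low-weight improvement: the fixed Bonferroni level for the healthcare worker tests is valid, but Holm's step-down method gives the same family-wise protection and never fewer rejections

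*Protocol article*

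**What the plan says.** Section 3.3 (Sample Size Calculation) of the protocol article sets the HW design: "Two independent HW groups will be assessed across three time points". On size it says: "An estimated 55 staff in each group (110 total) is required to achieve at least 80% power". The target is described only in general terms, as a change brought about by the programme, with no magnitude attached. The section then gives the multiplicity rule: "Applying the Bonferroni correction, the significance level for each test is adjusted to α = 0.05/9 = 0.0056".

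The article names no other multiplicity rule. Section 3.4 (Data Management and Analysis Plan) describes the efficacy analysis without one: "To explore efficacy outcomes, nonparametric analyses will be conducted across time points and between groups due to the potential of a small sample size".

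Section 3.2 (Efficacy Outcomes) defines several HW scores: four from the ISEI, one from the EOSS and three from the ProQOL ("Items will be averaged together to create three distinct scales"). Section 1.2 (Objectives) makes efficacy a secondary objective, pursued only if the feasibility result allows it.

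**The concern.** Single-step Bonferroni holds every test to 0.0056, including those examined after others have already been declared significant. Holm orders the p-values and relaxes the threshold after each rejection, with the same 5% guarantee. Where several outcomes really change, Holm can find some that Bonferroni misses.

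That situation is plausible here. The programme aims at several related HW scales, and the analysis section itself expects that the sample may be small. The results are also meant to inform a later cluster randomised trial, for which it helps to know which scales respond. At stake is the power to identify individual affected scales. Error control is not in question.

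**Working it through.** **Inputs from the article.** Family-wise level 0.05; nine tests; 55 per ward; power of at least 80% (all section 3.3).

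**Inputs assumed, because the article does not give them.** Two-sided tests; a standardised difference d, equal for every real effect; a common correlation of 0.3 to 0.5 between test statistics; normal test statistics as an approximation to the planned nonparametric tests.

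**1. The plan's own figure.** 0.05 / 9 = 0.005556, which rounds to 0.0056. It reproduces exactly.

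**2. Effect size implied by the plan.** With n per group, d = (z for 1 − α/2 + z for power) / √(n/2).
- Critical value for two-sided 0.05/9: 2.773. Value for 80% power: 0.842.
- d = (2.773 + 0.842) / √27.5 = 3.615 / 5.244 = 0.69.
- Using a t-test this becomes 0.70. For a Mann-Whitney test with relative efficiency 0.955 it becomes 0.72.

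So 0.7 SD is a fair working value for the planned design, but it is back-solved and not a figure from the article.

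**3. Power of one test at the fixed level.** The test statistic has mean d × 5.244.
- d = 0.7: mean 3.671, power = P(Z > 2.773 − 3.671) = 81.5%.
- d = 0.4: mean 2.098, power = P(Z > 2.773 − 2.098) = 25.0%.

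**4. Holm's thresholds for nine tests.** The i-th smallest p-value is compared with 0.05 / (9 − i + 1), stopping at the first failure: 0.00556, 0.00625, 0.00714, 0.00833, 0.0100, 0.0125, 0.0167, 0.0250, 0.0500. The first equals the plan's level, so the required sample size does not change.

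**5. Bonferroni against Holm.** The comparison used 200,000 simulated trials per setting, with nine equally correlated two-sided statistics at correlations 0.3 and 0.5. Average power per real effect:

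| Real effects among nine | d = 0.7, Bonferroni | d = 0.7, Holm | d = 0.4, Bonferroni | d = 0.4, Holm |
|---|---|---|---|---|
| 1 | 82% | 82% | 25% | 25% |
| 3 | 82% | 83% | 25% | 26% |
| 4 | 82% | 84% | 25% | 26% |
| 6 | 82% | 86% | 25% | 28% |
| 9 | 82% | 91–92% | 25% | 30–31% |

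- No Bonferroni rejection was lost under Holm in any simulated trial.
- The chance of any false positive under Holm was at most about 0.044 in these settings.
- The chance of at least one true rejection changed by less than 0.1 percentage point in every setting.

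**6. Dependence on the divisor.** The section 3.2 scores add up to 4 + 1 + 3 = 8, and the article does not explain the 9. The comparison is much the same with eight tests: if all eight are real at 0.7 SD, average power goes from about 83% to 92%.

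**The case against.** The strongest reply is that nothing here is wrong. Bonferroni is valid, 0.05/9 is computed correctly, and the 80% power claim stands beside that level, so no promised power is lost. This stands in full. A reader might infer that the plan contains an error or that the study is underpowered because of this choice. The article does not support either reading.

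A reader might also infer that power is given away for nothing. That is too strong on two counts. Bonferroni has simple simultaneous confidence intervals that match its tests, and Holm loses that match. The gain is also small unless many outcomes respond: nothing with one real effect, and about 1.5 to 5 points with three to six at 0.7 SD. The rise to 91–92% needs all nine tests to carry an equal effect of that size. If the nine were, for example, three instruments at three time points, the baseline comparisons could carry no intervention effect and that case could not arise.

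A third reply is that the sentence belongs to the sample size section, and that an analysis plan not shown may name another procedure. This stands in part. The wording sets the level for each test and is the only multiplicity rule in the article, so it can be read as governing the analysis, but the article does not settle this. As a planning level it is right in either case, because Holm starts from it.

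Finally, HW efficacy is exploratory, conditional on feasibility, and compares one ward with one ward. More rejections would not alter the feasibility conclusion. This stands, and it limits the weight.

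**Conclusion.** This is a cheap improvement of low weight. It is not a correction of an error. Holm gives the same 5% family-wise control as the stated rule under any dependence and can only add rejections; that does not depend on the effect size, the correlation or the number of tests.

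The size of the gain does depend on them. Under the assumptions above it runs from nil with one real effect to about 9 to 10 points of average power per test with all nine real at 0.7 SD, and to about 5 to 6 points with all nine real at 0.4 SD. The article gives no effect size and no estimate of how many scales will respond, so the upper end should not be quoted as the expected benefit. The chance of detecting at least one real effect is essentially the same under both rules, and the required sample size is identical.

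**What to change.** Leave the sentence in section 3.3 as it is, as the conservative planning level. Add to the quantitative analysis in section 3.4, before any HW outcome data are seen: *p-values for the HW efficacy tests will be adjusted by Holm's step-down method at a family-wise 5%.* If an analysis plan already names a procedure, align the two documents.

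The cost is one sentence and one call in R, the stated software: `p.adjust(method = 'holm')`. No extra participants are needed. The downside is that simple simultaneous confidence intervals no longer correspond exactly to the tests. Any intervals reported should be labelled as unadjusted, because such an interval can exclude zero while the Holm-adjusted test is not significant. Making the change after the data are seen would look data-driven, so the timing matters.

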### 3.4. Data Management and Analysis Plan

*Qualitative analysis.* Thematic analysis will be conducted on the feasibility of the EmpEd. The analytic interest is on how the experiences of participants are located within the wider socio-cultural context of the ward, which makes thematic analysis a suitable method for our purpose [34]. Thematic analysis will identify themes addressing feasibility issues, for instance, the usefulness of the programme, staff engagement and sustainability. Interview recordings and observational notes will be transcribed. To ensure consistency and accuracy of the analysis, two members of the research team will jointly analyse the data. The thematic analysis will follow Braun and Clarke’s [35] approach and will be completed by using NVivo 12.

The confidence in the quality of the qualitative data, analysis and interpretation will be assured by following the principles of trustworthiness in qualitative research [36]. Trustworthiness will be achieved by ensuring that multiple researchers have oversight of the data collection and analysis process. To ensure credibility of the data, only HWs who have participated in the EmpEd will be recruited into the focus groups, and verbatim quotes from these participants will be used to support themes/subthemes. The use of NVivo 12 to code the data will enhance opportunities for all researchers to evaluate the process of theme development, and it will also facilitate reflection on the analysis process.

*Quantitative analysis.* Descriptive and inferential statistical analysis will be conducted to assess the feasibility and potential efficacy of the EmpEd. Online responses will be registered through Qualtrics. Hard copy survey responses will be manually entered and error checked by looking at ranges and correlations. A minimum response rate of approximately 75% will be used as a cut-off point for the analysis (i.e., lack of completion of the empathy measures). Descriptive statistics will be summarised by using a number of observations, mean, and standard deviation for continuous data, and frequency and percentage for categorical data. To explore efficacy outcomes, nonparametric analyses will be conducted across time points and between groups due to the potential of a small sample size. Missing data will be reported as missing. All statistical analyses will be performed using R Statistical software.

*Academic Research Output.* The project will produce at least two academic research manuscripts, reflecting the feasibility and efficacy assessment of the EmpEd. These studies will draw comparisons with previous findings on the feasibility of immersive education programmes and their impact in the clinical setting.

*Protocol compliance.* The principal investigators will continuously monitor and overview the research process. Any violations and deviations of the protocol will be addressed on team meetings and recorded in Protocol Violation/Incident reports.

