## Abstract

Empathy is positively related to healthcare workers and patients’ wellbeing. There is, however, limited research on the effects of empathy education delivered in acute clinical settings and its impact on healthcare consumers. This research tests the feasibility and the potential efficacy outcomes of an immersive education programme developed by the research team in collaboration with clinical partners and a multidisciplinary advisory group. Healthcare worker participants in the intervention ward will receive an 8-week immersive empathy education. The primary outcome (feasibility) will be assessed by evaluating the acceptability of the intervention and the estimated resources. The secondary outcome (efficacy) will be assessed using a quasi-experimental study design. Non-parametric tests will be used to test healthcare worker participants’ empathy, burnout, and organisational satisfaction (within-group and across groups), and healthcare consumer participants’ satisfaction (between-group) over time. Despite growing interest in the importance of empathy in professional relationships, to our knowledge, the present pilot study is the first to explore the feasibility and efficacy of an immersive empathy education in New Zealand. Our findings will provide critical evidence to support the development of a randomised cluster trial and potentially provide preliminary evidence for the effectiveness of this type of empathy education.

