## 2. Method

### 2.1. Design

This quasi-experimental study of healthcare workers and healthcare consumers is a feasibility and pilot study to form the basis for a future, prospective cluster randomised trial (CRT). The single centre study will be conducted at one tertiary hospital in New Zealand. To minimise harm to participants, the key characteristics that will guide the ward selection are stable workforce, predictable patient population, and stable leadership. Based on local conditions, the Chief Nursing Officer will identify and select two wards (intervention and control ward) that meet these criteria. Although everyone on the wards will be invited to participate in the study, it is reasonable to expect that not everyone would want to be enrolled in the research. Thus, the wards are the study setting, and the groups are the enrolled participants on the wards.

Participants will be pre-allocated into four groups. Based on the participants’ location in the hospital, they will be either part of the intervention or the control group. Based on the participants’ position in the healthcare system, they will be either part of the HW group or the HC group. Participants in the HW groups will be constant during the study, while participants in the HC groups will differ across time points. HWs in the intervention ward/group will receive an 8-week immersive empathy education programme and the control ward/group will operate as usual during the research study. HCs will receive care, support and will interact with healthcare workers as usual in both wards/groups. HCs in the intervention ward/group will not be directly affected by the intervention; however, they will experience limited exposure to the education programme (e.g., seeing educational materials on the ward walls).

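### The healthcare-worker efficacy analysis names within-group and between-group tests but does not state the between-ward difference in change from baseline as the efficacy contrast

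*Protocol article*

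**What the plan says.** - **Analysis (section 3.4).** To explore efficacy, "nonparametric analyses will be conducted across time points and between groups due to the potential of a small sample size". No test is named.
- **Comparisons (Abstract).** For HWs, non-parametric tests of "empathy, burnout, and organisational satisfaction (within-group and across groups"). For healthcare consumers (HCs), tests of "satisfaction (between-group) over time".
- **Allocation (section 2.1).** Not random: "the Chief Nursing Officer will identify and select two wards (intervention and control ward) that meet these criteria". There is one ward per arm.
- **Who is measured (section 2.1).** "Participants in the HW groups will be constant during the study, while participants in the HC groups will differ across time points". HW data are therefore paired over time and HC data are not.
- **Timing (section 2.1).** Baseline in Weeks 1–3, second assessment in Weeks 13–15, follow-up in Weeks 27–30.
- **Sample size (section 3.3).** "Two independent HW groups will be assessed across three time points", with 55 per group, at least 80% power, and alpha 0.05/9 = 0.0056 per test. No effect size, SD, correlation or test is given.
- **Status (sections 1.2, 3.3 and 3.4).** Efficacy is the secondary objective and depends on the feasibility result. The HC part is treated as exploratory.

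No section mentions a ward-by-time contrast, a between-ward comparison of change scores, or baseline adjustment.

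**The concern.** The natural reading of the Abstract and section 3.4 is two kinds of comparison: each ward against itself over time, and one ward against the other. In a non-randomised two-ward study neither isolates the intervention.

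- The between-ward comparison at follow-up contains the intervention effect plus any difference the wards already had.
- The within-ward comparison contains the intervention effect plus anything that moved both wards, such as repeat surveying or hospital-wide events. Section 4 itself expects possible COVID-19 disruption.

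The difference in change removes a stable ward gap and a shared trend together. The data for it are already planned, since the same HWs are surveyed before the programme. Leaving it unstated also invites the inference that the programme worked because the intervention ward changed significantly and the control ward did not. At stake are the preliminary effectiveness evidence, the efficacy manuscript and the input to the future cluster randomised trial.

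**Working it through.** **The plan's own figures.** 0.05/9 = 0.00556, which rounds to the stated 0.0056. The 55 per group cannot be reproduced, because no effect size, SD, correlation or test is given. The power statement therefore does not show which contrast was intended.

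**Inputs.** From the protocol: 55 HWs per ward and alpha 0.05/9. Assumed, because the documents give no values: two-sided tests, normal scores with SD 1, a baseline-to-follow-up correlation ρ of 0.5 or 0.7, a stable ward gap of 0.3 or 0.5 SD, and a shared trend of 0.3 SD. There is no true effect. Two simulations were run: A with 55 per ward, ρ = 0.5 and 3,000 runs; B with 52 per ward (close to 138 × 0.75 / 2 = 51.75), ρ = 0.7 and 2,000 runs.

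**Rejection rates at alpha 0.0056, no true effect**

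| Test | Condition | A | B |
|---|---|---|---|
| Rank-sum between wards at follow-up | gap 0.3 SD | 10% | 9% |
| Rank-sum between wards at follow-up | gap 0.5 SD | 39% | 37% |
| Signed-rank within intervention ward | shared trend 0.3 SD | 24% | 44% |
| Intervention ward significant, control not | shared trend 0.3 SD | 19% | 24% |
| Rank-sum between wards on change | all conditions tried | 0.3–0.6% | 0.4% |

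At alpha 0.05, the follow-up test rejects in 31% to 34% of runs for a 0.3 SD gap and in 69% to 71% for a 0.5 SD gap.

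**Check by formula.** The critical value is z = 2.773, and rank tests have efficiency 0.955 relative to t tests.

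- Between wards at follow-up, the shift is gap × √(0.955n/2). For n = 55 and gap 0.3 this is 0.3 × √26.26 = 1.54, and P(Z > 2.773 − 1.54) ≈ 11%. For gap 0.5 it is 2.56, giving about 42%.
- Within a ward, the SD of change is √(2(1 − ρ)), and the shift is trend/SD × √(0.955n). For ρ = 0.5 and n = 55 this is 0.3/1 × √52.53 = 2.17, giving about 27%. For ρ = 0.7 and n = 52 it is 0.3/0.775 × √49.66 = 2.73, giving about 48%.

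These large-sample values lie slightly above the simulated ones and confirm their size.

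**Each bias touches one kind of test.** In simulation A at alpha 0.05, a shared trend alone leaves the between-ward test near 5%, and a ward gap alone leaves the within-ward test near 5%.

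**Power of the proposed contrast.** The detectable difference in change with 55 per ward and 80% power is (2.773 + 0.842) × √(2 × 2(1 − ρ)/(55 × 0.955)):

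| ρ | Detectable difference |
|---|---|
| 0.3 | 0.83 SD |
| 0.5 | 0.71 SD |
| 0.7 | 0.55 SD |

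A follow-up-only rank-sum test detects 0.71 SD whatever ρ is. The change score therefore gains power above ρ = 0.5, breaks even at 0.5, and loses below it.

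**What the contrast does not cure.** If each ward has its own random trend with an assumed SD of 0.2, the change-score test rejects in 27% of null runs at alpha 0.05 and in 10% at 0.0056 (55 per ward, ρ = 0.5).

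**The case against.** **The text is silent, not wrong.** A rank-sum test on change scores is itself a non-parametric analysis across time points and between groups. The sample-size sentence, with two groups and three time points, is compatible with a group-by-time test. A fuller protocol or analysis plan may name it. This stands against the stronger reading that a reader might infer, namely that the plan commits to separate tests only and can never estimate the difference in change. The documents do not say that. What survives is that the article does describe its comparisons, in two places, and the contrast that answers the question is in neither.

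**The small-sample reason is not a contradiction.** One might hold that it conflicts with 55 per ward. It does not: section 3.4 speaks of a potential small sample, section 4 warns of high drop-out, and 55 is a target. Nor does the plan leave no route to an estimate, because means and SDs will be reported.

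**The sizes are assumed.** This stands. The gaps, trend and correlation have no source in the documents, and the within-ward rate nearly doubles between ρ = 0.5 and 0.7. The figures show that the bias can matter, not that false positives will occur.

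**The remedy is partial.** This also stands. With one ward per arm, no analysis separates the programme from a trend peculiar to that ward.

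**Efficacy is secondary.** Feasibility is the primary objective, and no stated progression rule uses these p-values. That lowers the importance of the point but does not remove it.

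**Conclusion.** The point holds at moderate severity. The protocol names only within-group and between-group comparisons for HW efficacy and does not state the between-ward difference in change. On the natural reading, and with no true effect, a stable ward gap of 0.3 to 0.5 SD can make the follow-up comparison significant in about 9% to 39% of studies at alpha 0.0056. A shared 0.3 SD trend can make the within-intervention-ward comparison significant in about 24% to 44%. Both ranges rest on assumed gaps, trend and correlation, and each bias affects only its own kind of test. A between-ward test of change stays near nominal provided that the ward gap is stable and any trend is common to both wards. It would be wrong to conclude that the planned analysis must mislead, or that changing it would make two selected wards equivalent to a randomised comparison.

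**What to change.** 1. State in section 3.4 that the HW efficacy contrast for each scale is the between-ward difference in change from baseline to Weeks 13–15, then to Weeks 27–30. A rank-sum test on individual change scores, with a Hodges–Lehmann estimate and 95% CI, keeps the analysis non-parametric. A mixed model with ward, time, ward-by-time and a participant random intercept is an optional alternative.
2. Report within-ward changes descriptively, without using significance in one ward and not in the other as evidence of effect.
3. For HCs, use an exploratory ward-by-period contrast of independent samples. It will be imprecise: with 25 per ward per time point, its standard error is √(4/25) = 0.40 SD, so the 95% CI is about ± 1.96 × 0.40 = 0.78 SD.
4. Say in the report that, with one ward per arm, ward-specific trends remain confounded with the intervention.

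**Cost.** Wording only. There is no new data collection, and R, the software already named, can do the analysis. HW records must be linked over time, which the self-chosen identifier code in section 2.3 appears to allow. The statistical price is no gain in power if the baseline-to-follow-up correlation is about 0.5, and some loss if it is lower.
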